#### 11.4.3 Secondary analysis

For categorical outcomes, we will additionally calculate relative risk differences between groups. We will calculate odds ratios from multiple logistic regression models adjusting for the type of monitoring and type of treatment as appropriate. For repeatedly measured categorical outcome variables (virological suppression <50 copies/mL), we will consider a mixed effects logistic regression with a random intercept on the subject to account for within-patient correlations.

For repeatedly measured continuous outcome variables, we will also consider all measurements in a linear mixed effects regression model to account for within-patient correlations. Finally, we will analyse development over time by exploring the functional relationship between outcome and time using fractional polynomials and a treatment-by-time interaction term.

Moreover, we will evaluate all outcomes in crude analyses not adjusting for type of monitoring or type of treatment. Binary outcomes will be compared by the Chi-squared or Fisher's exact test, continuous outcomes by the Student t-test.

Cost-effectiveness of treatment arms (incremental cost-effectiveness ratio) will be calculated by taking the difference in mean costs between patient-centered arm and standard monitoring arm, and between DTG + FTC dual therapy arm and cART arm, and dividing them by the difference in time to loss of virological response (TLOVR) between the study arms. Difference in TLOVR will be assessed by comparing the area under the patient-centered and standard monitoring Kaplan-Meier curves, and under the DTG+FTC and cART Kaplan-Meier curves. Generalised lo-rank test will be used to compare times between groups.

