| Health related costs assessment                                                                                            |   |   |                                                                                     |     |     |     | X |

 Safety serum chemistry includes CK, creatinine, ASAT, ALAT, gamma-GT, alkaline phosphatases; glucose and lipid profile.

 Patients with HIV-RNA between 20 and 99 copies/ml will benefit from another HIV-RNA measurement after 6 weeks (± 5 days). Patients with HIV-RNA ≥ 100 copies/ml will benefit from another HIV-RNA measurement after 2 weeks (± 5 days).

\* CD4-count, full blood count and safety serum chemistry will be performed on a 3-monthly basis for patients randomized in the standard monitoring arm. Patients randomized in the patient-centered monitoring arm will benefit from these routine tests on a yearly basis (i.e. at day 0 and week 48).

\* Patients new to DTG will benefit from CK measurement and from hepatic safety serum tests, i.e. ASAT, ALAT, gamma-GT, alkaline phosphatases, at week 6 whatever monitoring arm.

† Diabetic patients under concomitant metformine and dolutegravir will benefit from blood glucose and creatinine measurements at weeks 6, 12, 24 and 36 whatever monitoring arm.

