### **Patient-centered monitoring**

Randomization will also allocate patients into the following two groups:

- Standard monitoring arm: patients randomized in this arm will continue a standard 12-weekly routine immunological and safety blood monitoring, including CD4 cell count, lipids and glucose, renal and hepatic function tests, creatine kinase at their affiliated SHCS sites.
- Patient-centered monitoring arm: patients randomized in this arm will have immunological and safety blood analyses (CD4 cell count, lipids and glucose, renal and hepatic function tests, creatine kinase) performed at screening and at week 48. Additional safety blood tests will be performed in case of signs and symptoms as indicated by the physician. In addition, patients will have to choose at least one of three alternative options for the conduction of study visits, venipuncture and drugs delivery at weeks 6, 12 and 36, see section 8.1.1. Patients will also have the opportunity to change or give their opinion on the alternative option(s) chosen if they find it non convenient during the study. Changes will be possible at week 24; satisfaction will be assessed at week 12, 24, 36 and 48.

Importantly, all interventions or blood measurements potentially related to adherence (affecting the primary endpoint) will be identical between the study arms (see section 8.4).

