|-------------------------------------------------------------------------------------------------------------------------------------------------------------------------|----------------------------------------------------------------------------------------------------------------------------------------------------------------------------------------------------------------------|
| All visits at SHCS center                                                                                                                                               | Weeks 24 and 48 visits at SHCS center                                                                                                                                                                                |
| WHERE                                                                                                                                                            | Weeks 6, 12, 36 according to patient choice (see HOW below)                                                                                                                                                          |
|                                                                                                                                                                         |                                                                                                                                                                                                                      |
| Week 6:
- HIV-RNA measurement only
Weeks 12, 24, 36 and 48 visits:
- Complete blood analysis with HIV-RNA, CD4 count, full blood count, safety serum chemistry | Week 6, 12, 24, 36:
- HIV-RNA measurement only
Week 48:
- Complete blood analysis with HIV-RNA, CD4 count, full blood count, safety serum chemistry                                                         |
| WHAT                                                                                                                                                             |                                                                                                                                                                                                                      |

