#### 11.4.2 Primary analysis

As a first step in this factorial trial, we will test for an interaction between the type of drug treatment and the monitoring type in order to assess if treatment effect is different depending on the type of monitoring. If the test is non-significant we will combine the two types of monitoring for the drug therapy comparison and the two drug therapies for the monitoring comparison. Otherwise, the trial will be analysed as a four-arm trial with a hierarchical testing approach.

For the primary comparison of the primary outcome between the two treatment arms, we will obtain the proportion of patients with viral suppression for 48 weeks in each arm, and compute a Mantel-Haenszel risk difference (DTG+FTC - cART) stratified for the monitoring type with a two-sided 95% confidence interval (107). If the lower confidence limit is higher than -12% we will conclude non-inferiority. If the lower confidence limit is below -12% we will conclude that DTG + FTC is potentially inferior to cART.

For the secondary comparison of the primary outcome between the two monitoring arms, we will calculate a Mantel-Haenszel test statistics and Mantel-Haenszel risk difference (DTG+FTC - cART) stratified for the type of treatment.

Secondary categorical outcomes (proportions of virological suppression <50 copies/mL both as a standard proportion and as FDA snapshot, of loss of future treatment options, of adverse events, of serious adverse events, of CSN adverse events, of CNS symptoms) between the DTG+FTC and cART groups, and between the patient-centered and standard monitoring groups will also be analysed using the Mantel-Haenszel test statistics and Mantel-Haenszel risk difference (DTG+FTC - cART) stratified for the type of monitoring and type of treatment, respectively.

For continuous outcome variables (CD4 count, HIV-DNA level, total cholesterol, high-density lipoproteine, triglycérides, low density lipoprotein-cholesterol, glucose, Framingham-calculated cardiovascular risk, glomerular function rate, weight, health-related quality of life, treatment satisfaction), we will compare the mean values at 48 months between the DTG+FTC and cART treatment groups and between the patient-centered and standard monitoring groups using linear regression adjusted for the type of monitoring and type of treatment, respectively.

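### The supportive mixed models use all laboratory measurements, although the two monitoring arms are not tested on the same schedule between baseline and week 48

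*Protocol*

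**What the plan says.** Section 11.4.2 lists the continuous outcomes, among them CD4 count, lipids, glucose, Framingham risk and glomerular function. It compares their means at the final time point (printed as 48 months; section 5.2 defines these outcomes at week 48). The comparison is made between drug arms and also "between the patient-centered and standard monitoring groups using linear regression adjusted for the type of monitoring and type of treatment, respectively".

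Section 11.4.3 adds a supportive analysis: "we will also consider all measurements in a linear mixed effects regression model to account for within-patient correlations". It then describes development over time by "exploring the functional relationship between outcome and time using fractional polynomials and a treatment-by-time interaction term". It does not restrict the model to scheduled values or to time points that both arms share. The rules in section 11.5 concern missing values at the final time point.

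The laboratory schedule differs by monitoring arm:

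- **Standard monitoring:** CD4, blood count, chemistry, glucose and lipids in every patient at weeks 12, 24 and 36 (sections 9.3.5 and 9.3.6).
- **Patient-centered monitoring:** these tests are "performed at screening and at week 48" (section 6.1). Table 1 in section 8.1.1 gives "HIV-RNA measurement only" for weeks 6 to 36.
- **Exceptions in the patient-centered arm:** "Additional safety blood tests will be performed in case of signs and symptoms as indicated by the physician" (section 6.1), and "Diabetic patients under concomitant metformine and dolutegravir will benefit from blood glucose and creatinine measurements" at weeks 6, 12, 24 and 36 in either monitoring arm (Study schedule footnote).

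**The concern.** Read literally, the model sets a fully observed arm against a small, selected part of the other arm at weeks 12 to 36. A mixed model handles absent values well when the data and terms in the model explain why they are absent. That is doubtful here. A symptom-triggered test depends on the patient's state on the day, and metformin use is not a stated model term.

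Sections 4.3 and 4.4 make the safety of the monitoring strategy an objective. Section 4.4 assesses it through CD4, cholesterol, Framingham risk and glomerular function, among other things. A mid-study difference in eGFR or glucose produced only by who was tested could be read as harm or benefit of reduced monitoring. With two routine time points, the patient-centered arm also cannot support a fractional-polynomial curve. Its shape would come from the other arm, from model form, or from the selected values.

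**Working it through.** The plan states no figure on this point, so there is none to reproduce. The check is of the schedule and of how a random-intercept model treats selected values.

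**1. Values available at weeks 12, 24 and 36.** Section 11.2 gives 92 patients per monitoring arm.

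- Standard arm: 92 x 3 = 276 scheduled values per laboratory outcome.
- Patient-centered arm, CD4 and lipids: no scheduled values.
- Patient-centered arm, glucose and creatinine: metformin patients on dolutegravir only. Assuming 46 patients on dolutegravir and 5-10% on metformin, this is 46 x 0.05 x 3 = 6.9 to 46 x 0.10 x 3 = 13.8 values.

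**2. A stable difference (metformin users).** Suppose metformin users differ from the other patients by a constant d, and a fraction p of patients are users. Their baseline and week-48 values are in the model, so the random intercept absorbs most of d. With between-patient variance B and within-patient variance W, what is left in the mid-study contrast is about

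(1 - p) x d x W / (2B + W).

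- Standardised scale, assuming W = 0.36, B = 0.64 + p(1 - p)d² and d = 2. For p = 0.05, B = 0.83 and the bias is 1.9 x 0.36 / 2.02 = 0.34 SD. For p = 0.10, B = 1.00 and the bias is 1.8 x 0.36 / 2.36 = 0.27 SD.
- Simulation with no true monitoring effect gave 0.28-0.35 SD, falsely significant in 17-19% of trials. The raw mean difference was 1.9-2.0 SD.
- eGFR, assuming SDs of 12 between and 6 within patients: W / (2B + W) = 36 / 324 = 0.11, so about 11% of the gap remains. Simulation gave -1.3 ml/min mid-study, which corresponds to a gap of about 12 ml/min (12 x 0.11 = 1.3). It was significant in 6.5% of trials. As one averaged post-baseline effect the shift was -0.2 ml/min.

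**3. A temporary difference (symptom-triggered tests).** Baseline and week-48 values do not predict a temporary dip, so nothing absorbs it. The eGFR simulation used the same SDs and no true effect. It assumed that 10-20% of patient-centered patients had one triggered test, 5 or 10 ml/min below their usual level, and that the standard arm had no dips.

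- Mid-study contrast: -4.8 and -10.1 ml/min, in effect the whole dip.
- Falsely significant in 38-77% of trials (dip 5) and 90-100% (dip 10), depending on the fraction tested and on whether the model lets the arms differ at baseline. Without a dip the rate was 4-7%.
- One averaged post-baseline effect: -0.6 to -2.2 ml/min, significant in 6-50% of trials against 4% without a dip.

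On the standardised scale, metformin selection (5%) was combined with triggered tests (5-10% per visit, 0.5-1 SD higher). The same shifts were given to standard-arm patients. The bias was 0.42-0.81 SD, with 57-100% false significance. When triggered values did not differ and there were no metformin users, the bias was about 0.

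**4. Week 48.** The contrast stayed within 0.02 SD of zero in every standardised scenario, with 3-8% false positives. The eGFR model restricted to baseline and week 48 was unbiased, with 6.5% false positives.

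**5. Drug contrast.** With 46 per cell, 10% on metformin and a 1 mmol/l glucose rise in those patients, the estimate was 0.13 against a true 0.10 mmol/l.

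**The case against.** Four points stand against this.

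- **The named interaction is with treatment.** Section 11.4.3 speaks of "using fractional polynomials and a treatment-by-time interaction term", and elsewhere the protocol uses treatment for the drugs and monitoring for the other factor. No monitoring-by-time term is written down. This stands for the interaction. It does not settle the mixed model itself, because section 11.4.2 compares the same outcomes by monitoring group and 11.4.3 adds all measurements without limiting that.
- **Triggered results may never enter the analysis data.** Section 9.2.3 records extra visits by date and reason. Section 10.1.1 reports listed laboratory abnormalities as adverse events only from grade 3. An extra-visit worksheet exists (section 12.1.2), but its content is not shown. This stands, and the large figures depend on it. The metformin tests do not, because they are scheduled study assessments.
- **The large simulated bias restates its input.** For eGFR this is largely true: the contrast equals the assumed dip, and the standard arm was given none. If the standard arm dipped in 10% of patients at each visit, a dip of 5 would still leave 5 x 0.9 = 4.5 ml/min. The standardised simulation, with equal symptom rates in both arms, points the same way.
- **This is detail for the statistical analysis plan.** Section 11.4.6 does defer detail to that plan. But the protocol already states a rule, and for these outcomes it is too wide.

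A reader might infer that all laboratory data between baseline and week 48 in the patient-centered arm come from unwell or diabetic patients. They do not: HIV-RNA is measured in everyone, and patients new to dolutegravir have CK and liver tests at week 6 in either arm. Neither belongs to the listed continuous outcomes. Nor are the metformin tests triggered by the result. They follow from concomitant treatment, so their selection is on a patient characteristic and not on the current value.

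**Conclusion.** The point holds for one supportive analysis. A monitoring contrast for laboratory outcomes from the mixed model on all measurements is open to selection bias, and the model cannot estimate a mid-study curve in the patient-centered arm. Selection is clearest for glucose and GFR. For CD4 and lipids the problem is mainly extrapolation.

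The size is not fixed by the protocol. With metformin selection alone it is small in the eGFR model (-1.3 ml/min mid-study, 6.5% significant) and moderate under the harsher standardised assumptions (0.28-0.35 SD, 17-19%). It is large only if symptom-triggered values are included and differ systematically. The SDs, metformin prevalence, test frequency and dips are all assumptions.

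A reader might go further and infer that the trial's conclusion on the safety of reduced monitoring is biased, or that a false mid-study difference is to be expected. The documents do not support that. The defined outcomes and the main comparison are at week 48, where no bias appeared. The drug contrast is only slightly affected, and the protocol does not state that triggered results are analysed. The text should be corrected, but the main results are not threatened.

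**What to change.** Add to section 11.4.3, or to the statistical analysis plan, for CD4, lipids, glucose, Framingham risk and glomerular function:

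- Limit mixed-model monitoring contrasts to time points scheduled for everyone in both monitoring arms, that is screening/baseline and week 48.
- Use week 12, 24 and 36 values, the fractional polynomials and the drug-by-time term only within the standard-monitoring arm.
- Flag and exclude from these models symptom-triggered values and values taken only because of dolutegravir with metformin. In the standard arm, metformin patients keep their routine week 12-36 values; only their extra week-6 values drop out.
- Keep the full longitudinal model for outcomes on a common schedule in all arms, such as quality of life and weight.

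The cost is a few sentences and a flag on unscheduled or selective laboratory values. The mid-study drug curves would rest on the standard-monitoring half of the trial (184 / 4 = 46 patients per drug arm), where all the unselected mid-study values lie. The one loss is a mid-study laboratory curve for the patient-centered arm, which the design cannot provide anyway.

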| Study design:                   | 
This is a pragmatic multicentre, 2x2 factorial randomized controlled trial with 1:1:1:1 randomization to switching to DTG-based maintenance dual therapy in association with FTC or continuation of cART, and to patient-centered monitoring or continuation of standard monitoring.
 
The randomized comparisons will examine whether DTG + FTC dual therapy is non-inferior in terms of viral suppression compared to standard therapy, and whether patient-centered monitoring is cost-saving and acceptable compared to standard monitoring.
 
Patients will be followed during 48 weeks.
 
A sample size of 92 patients in each group (DTG + FTC dual therapy and standard cART) will be required to demonstrate non-inferiority with a non-inferiority (NI) margin of 12%.
                                                                                                                                                                                                                                                                                                                                                                                                                                                                                                                             |

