Seventy percent of HIV-infected patients in Switzerland are integrated into the work force and most are able to work full time (42). In this situation, a patient-centered monitoring may be more suitable in the long-term. As a second objective, we propose to assess if a patient-centered monitoring that offers alternative options for the delivery of study visits, laboratory tests and drugs is cost-saving (first goal) and acceptable (second goal) , without jeopardizing safety, compared to routine monitoring.

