### 5.2 Secondary Outcomes

1. Proportion of patients maintaining HIV suppression defined as HIV-RNA <50 copies/ml throughout 48 weeks (+/- 21 days). A single blip defined as HIV-RNA <200 copies/ml during the study period is allowed as long as this value is followed by HIV-RNA <50 copies/ml;
2. Proportion of patients with HIV-RNA < 50 cp/ml at week 48 by FDA snapshot analysis; Proportion of patients experiencing loss of future drug options defined as new intermediate or high-level resistance to one or more drugs to which the patient's virus was considered sensitive at trial entry;
3. Time to loss of virological response (TLOVR) up to week 48 defined as the first of the two-confirmed HIV-RNA >100 copies/ml (at least two weeks apart);
4. Change in CD4 cell count from baseline to week 48 +/- 21 days;
5. Change in HIV-DNA level from baseline to week 48 +/- 21 days;
6. Change in lipidic profile (total cholesterol, high density lipoprotein-cholesterol, triglycerides, and low density lipoprotein-cholesterol) from baseline to week 48 +/- 21 days;
7. Change in glucose profile from baseline to week 48;
8. Change in Framingham-calculated cardiovascular risk from baseline to week 48;
9. Change in glomerular function rate from baseline to week 48;
10. Proportion of patients with an adverse event throughout week 48;
11. Proportion of patients with a serious adverse event (SAE) throughout week 48;
12. Proportion of patients with a CNS adverse event throughout week 48;
13. Proportion of patients new to DTG with CNS symptoms at 2 and 6 weeks after starting DTG;
14. Change in patients' health-related quality of life from baseline to weeks 12 and 48;
15. Assessment of patient's monitoring satisfaction from baseline to weeks 24 and 48 for patients in the patient-centered monitoring arm;
16. Assessment of the global satisfaction of the monitoring at week 48 for all patients (regardless of the randomisation arm);
17. Proportion of patients in the patient-centered monitoring arm expressing willingness to change monitoring options throughout 48 weeks;
18. Assessment of patient's treatment satisfaction at week 48;
19. Assessment of ARV treatment in the post study;
20. Study satisfaction at week 48;
21. Cost-effectiveness of study arms at 48 weeks;
22. Changes in patient weight from baseline to week 48.

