### 11.2 Determination of Sample Size

The first sample size calculation was based on the primary outcome for the comparison between DTG + FTC dual therapy and standard cART, i.e. the comparison between the proportions of patients in the two arms maintaining virologic suppression, using a two-sample proportion test (96). The following assumptions were made:

- Power 80%
- Significance level 0.025 (one-sided Z test of non-inferiority)
- 97% of patients with conventional cART will be virologically suppressed at week 48 (<100 copies/ml)
- 94% of patients on DTG + FTC dual therapy will be virologically suppressed at week 48 (<100 copies/ml)
- Non-inferiority margin of 12% (as in previous non-inferiority trials)(97-104). We chose 12% noninferiority margin because there is no difference in terms of resistance acquisition between 10% and 22% virological failure.

Sample size of 83 patients in each group (total sample size, 166 patients) to achieve 80% power to detect a non-inferiority margin difference between the group proportions of -0.12 was calculated. The power was computed for the case when the actual cART group proportion is 97% and the actual DTG + FTC dual therapy group proportion is 94%. To allow for at least 10% loss to follow-up and also for the randomisation in two steps in this 1:1:1:1 trial, we will aim to recruit **a total of 184 patients**.

The second sample size calculation was based on the primary outcome for the comparison between simplified monitoring and standard monitoring, i.e. the comparison between mean direct costs in the two arms (105). The following assumptions were made:

- Significance level 0.05 (two-sided t-test)
- Direct costs are CHF 25,000 per year (standard deviation (SD) CHF 8,000) with conventional monitoring
- SDs are equal in the two groups (CHF 8,000)

With sample sizes of 92 patients in each group, we will have approximately 55% power to detect a 10% difference in costs, and 99% power to detect a 25% difference in costs. We will also have substantial power to detect small-to-moderate differences in many of the secondary outcomes, e.g. changes in CD4 cell counts or health-related quality of life. The exceptions are rare outcomes such as adverse events, resistance or clinical complications for which the statistical power to detect differences will be low.

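### The cost-effectiveness ratio in 11.4.3 divides by a TLOVR difference that the design expects to be small or zero, so it is too imprecise to interpret for the drug factor and has no stable value or sign for monitoring.

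*Protocol*

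**What the plan says.** Cost-effectiveness of the study arms at 48 weeks is secondary outcome 21 in Protocol section 5.2. Section 11.4.3 fixes the statistic for both the drug and the monitoring comparison: the difference in mean costs is taken, "dividing them by the difference in time to loss of virological response (TLOVR) between the study arms". It also fixes how the denominator is measured: "Difference in TLOVR will be assessed by comparing the area under the patient-centered and standard monitoring Kaplan-Meier curves", and likewise for the two drug arms. Section 5.2 gives the event and the horizon: "Time to loss of virological response (TLOVR) up to week 48 defined as the first of the two-confirmed HIV-RNA >100 copies/ml". The protocol text gives no rule for a denominator that is zero or changes sign.

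The planning assumptions bear on that denominator. Section 11.2 assumes "97% of patients with conventional cART will be virologically suppressed at week 48" and 94% on the dual therapy. The synopsis (Statistical Considerations) assumes 92% in both arms. No virological effect of monitoring is quantified anywhere. Section 6.1 (Patient-centered monitoring) keeps everything related to adherence, and so to the primary endpoint, the same across arms.

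**The concern.** A ratio is usable only if its denominator is reasonably well separated from zero. The drug comparison is a non-inferiority question with very few expected failures, and the monitoring factor is meant to save money at unchanged virological control. Few patients should lose response within 48 weeks, so the two curves should nearly coincide. When the area between them is a fraction of a week and its sampling error is of the same order, dividing a cost difference by it gives a number governed by where a handful of failures fall.

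The second problem is one of reading. A positive ratio can mean cheaper with less response time, or dearer with more. A negative one can mean cheaper with more, or dearer with less. The ratio alone does not say which. What is at stake is whether the planned summary can answer the cost-effectiveness question for either factor.

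**Working it through.** **1. The plan's own figures.**
- Non-inferiority size, 97% vs 94%, margin 12 points, one-sided 0.025, 80% power: n = (1.960 + 0.842)² × (0.97×0.03 + 0.94×0.06) / (0.12 − 0.03)² = 7.85 × 0.0855 / 0.0081 ≈ 83 per group, as stated.
- Cost power at 92 per group, SD CHF 8,000: the standard error is 8,000 × √(2/92) ≈ CHF 1,180. A CHF 2,500 difference (10% of 25,000) has about 56% power, against the stated 55%.

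The planning inputs are therefore read correctly.

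**2. Expected denominator, drug factor.** A patient who fails at week t loses 48 − t weeks of area. The protocol gives neither a TLOVR event rate nor failure times. The week-48 suppression rates stand in for the event rate, and the timing is varied. The expected difference (DTG+FTC minus cART) is −(0.06 − 0.03) × mean loss.

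| Timing of failures | Mean loss (weeks) | Expected difference (weeks) |
|---|---|---|
| All at week 6 | 42 | −1.26 |
| Equally at weeks 6, 12, 24, 36, 48 | (42+36+24+12+0)/5 = 22.8 | −0.68 |
| All at week 36 | 12 | −0.36 |

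A constant hazard gives −0.73. The ceiling is 0.03 × 48 = 1.44 weeks. The difference exceeds one week only if the excess failures fall on average before about week 15 (1/0.03 = 33 weeks lost). Section 3.4 reports that in one monotherapy trial most failures came after week 24, which would imply 0.72 week or less.

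**3. Sampling error, 92 per arm, no dropout, failures spread equally over the visits.** The mean squared loss is (42² + 36² + 24² + 12² + 0)/5 = 756. The variance per patient is p×756 − (p×22.8)².
- 97/94: (22.21 + 43.49)/92 = 0.714, SD 0.845 week.
- 95.5% in both arms (midpoint of 97 and 94, used for monitoring): 2 × 32.97/92 = 0.717, SD 0.847 week.
- 92% in both arms: 2 × 57.15/92 = 1.242, SD 1.115 weeks.

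The full distribution of the difference under this pattern is:

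| Scenario | Mean | 95% range (weeks) | Positive | Exactly zero |
|---|---|---|---|---|
| Drug, 97/94 | −0.68 | −2.4 to +0.9 | 19% | 2.6% |
| Monitoring, 95.5/95.5 | 0 | −1.7 to +1.7 | 48% | 3.5% |
| Either factor, 92/92 | 0 | −2.2 to +2.2 | 49% | 2.4% |

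If failures are instead spread in proportion to visit intervals and both arms are at 97%, an exactly zero denominator occurs in about 7% of trials.

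**4. Leverage of single patients.** One failure at week 6 moves an arm's mean by 42/92 = 0.46 week, and one at week 12 by 36/92 = 0.39. Together that is 0.85 week, more than the expected drug difference of 0.68.

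**5. Effect on the ratio.** These simulations include sampling error in costs (SD CHF 8,000). They assume a true saving of CHF 2,500, which is the reviewer's assumption for both factors. The 95% range of the ratio, in CHF per week, is:
- drug, 97/94: about −33,000 to +33,000 under a constant hazard, and −23,000 to +27,000 when failures are detected at visits;
- monitoring, 95.5/95.5: about −46,000 to +52,000, and −29,000 to +31,000 respectively.

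With a monitoring saving of CHF 6,250, where the cost comparison has over 99% power, the constant-hazard range is still about −116,000 to +112,000. The instability comes from the denominator, not from noisy costs.

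**The case against.** Several points on the other side are fair.

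- **The drug ratio is not pure noise.** A reader might infer that neither its size nor its sign carries any information. Under 97/94 the sign is negative in about 80% of trials. That is imprecision. Only monitoring, or the 92/92 assumption, gives a coin toss.
- **The size rests on assumptions.** A reader might infer that the protocol itself predicts a difference under one week. It does not. Failure timing is not given, and suppression at week 48 is not the same endpoint as confirmed rebound. The range above is the answer to that.
- **Zero for monitoring is not stated.** Section 3.1 asks only that monitoring work "without jeopardizing safety, compared to routine monitoring", which concerns safety. Section 6.1 is the better support, and zero remains an assumption.
- **The components are partly reported already.** Section 11.4.2 plans a regression of mean costs by monitoring strategy, and Kaplan-Meier and Cox analyses of TLOVR. Section 11.4.3 compares the areas. A careful reader could work out the quadrant. This softens the sign problem but does not make the ratio interpretable.
- **Uncertainty methods may sit in an analysis plan.** That is so, and their absence is no finding. The choice of the ratio is different, because the protocol fixes it.

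**Conclusion.** The point holds as a criticism of the statistic chosen in 11.4.3. For the drug comparison the expected denominator is about −0.4 to −1.3 weeks. With failures spread over the visits it is about −0.7 week, its 95% range crosses zero, and it is zero or positive in about 22% of trials. The ratio is then too imprecise to interpret. For monitoring, or under 92% in both arms, the expected denominator is zero, the sign is about 50:50, and the ratio has essentially no stable value. Across the rates and visit patterns tried, about 2 to 7% of trials yield no ratio at all.

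This rests on week-48 suppression as a proxy for TLOVR events, assumed failure times, 92 per arm with no dropout (censoring would widen the spread), and no monitoring effect on virology. The conclusion is the same under the section 11.2 rates and the synopsis rates; the difference between those two is a separate matter. A reader might also infer that the trial's cost conclusion is at risk. It is not: the primary cost and efficacy comparisons do not use this ratio.

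**What to change.** In section 11.4.3, make the cost-effectiveness result for each factor the incremental cost and the incremental response time (difference in area to week 48). Obtain their uncertainty jointly by resampling patients, and show it on the cost-effectiveness plane. Add incremental net monetary benefit over a pre-stated range of values per week of maintained response.

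If a ratio is still shown, make it descriptive, with its quadrant and the joint uncertainty beside it. Do not make its reporting conditional on the effect interval excluding zero. With mean 0.68 and SD 0.84 that would happen in only about 13% of trials for the drug factor, and it would select the trials with the largest apparent differences.

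The cost is a bootstrap on data already being collected. The small downside is that a range of values per week of response must be chosen, and the protocol offers none.
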